### Recruitment Strategy and Patient Screening

Before the study begins, baseline characteristics and medical history will be recorded for all potential participants. Those who meet the eligibility criteria (Textbox 1) will receive detailed study information, including the study purpose, procedures, risks, and benefits. Informed consent will then be obtained voluntarily. Eligible subjects who meet all criteria will be formally enrolled. They will then be assigned to treatment groups according to the site’s randomization scheme. After entering the electronic randomization system, all subject data will be locked. Each operation within the system will be automatically recorded in audit trails for monitoring purposes (Figure 1).

Eligibility criteria for the study.

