**Figure 2 figure2:**
[figure not shown]
Main equipment of the navigation system.

It must be emphasized that although the novel navigation system can provide visual assistance for fracture reduction, manual reduction will be exclusively used in this study to minimize variability and potential bias, thereby safeguarding study quality. The navigation system will be primarily used for surgical planning and screw placement.

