### Randomization and Blinding

This is a single-blind trial in which patients and outcome assessors will be blinded to treatment allocation, while operating surgeons cannot be blinded because of the distinct intraoperative workflows associated with the navigation system and the freehand technique. Patients will remain blinded to their group assignment throughout the surgical procedure and the entire 12-month follow-up period, with the specific technique disclosed only after completion of all outcome assessments unless early unblinding is required for safety reasons. Radiographic assessors and functional outcome assessors will be blinded to group allocation, as all imaging studies and clinical assessments will be coded with unique participant identifiers and conducted without access to treatment assignment records. The primary statistical analyst will remain blinded until the final database is locked and all predefined analyses are completed, with group codes revealed only after the statistical analysis plan has been fully executed. Emergency unblinding may be performed by the principal investigator in the event of a serious adverse event for which knowledge of the intervention is essential for patient management, and any such event will be documented and reported.

Randomization will be performed by the coordinating center using a centralized computer-generated system with permuted blocks of 4 to ensure balanced allocation across treatment groups. Assignment details will be distributed to all participating sites via sequentially numbered, sealed opaque envelopes. All surgical procedures will be performed in accordance with the assigned randomization.

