#### Intervention Group: NS+TCS Fixation

Following successful anesthesia, the patient is positioned supine on a traction table. Satisfactory reduction of the fracture fragments is achieved under G-arm fluoroscopic guidance. The operative field is routinely prepared and draped in a sterile fashion.

Two guide pins are inserted, one at the anterior superior iliac spine and another at the lateral femoral condyle, to serve as anchoring points. A navigation reference array is then mounted. The exposed ends of the guide pins are trimmed to an appropriate length to avoid interference with subsequent fluoroscopic imaging. Image registration markers are positioned anteriorly and laterally to the hip joint. Standard anteroposterior and lateral hip radiographs are acquired and uploaded to the navigation system workstation for preoperative trajectory planning for TCS placement. An inverted triangular configuration is selected for dispersed screw placement. After calibration of the navigated drill sleeve, the planned trajectories are used to percutaneously insert 3 guide wires sequentially into the femoral neck and head through small skin incisions. Subsequently, TCS are inserted over the guide wires. Fluoroscopic confirmation is obtained to verify satisfactory screw length and position.

Upon confirmation of adequate fixation, the reference guide pins at the anterior superior iliac spine and lateral femoral condyle are removed. The surgical incisions are irrigated and closed in layers (Figure 3).

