### Outcomes and Measures

#### Primary Outcome

The total number of intraoperative fluoroscopic images will be recorded for both groups. This includes each anteroposterior and lateral view obtained, starting from fracture reduction. To minimize observer bias, fluoroscopic counts will be categorized and analyzed separately for fracture reduction, navigational positioning, and implant placement.

Fluoroscopy frequency was selected as the primary outcome for this superiority trial for the following reasons. First, the number of intraoperative fluoroscopic images is an objective, quantifiable, and operator-independent measure that directly reflects the efficiency and precision of guide wire and screw placement. Second, reducing radiation exposure is a major clinical advantage of navigation-assisted surgery, as it lowers occupational radiation risk for surgical staff and potential patient harm. Finally, fluoroscopy frequency is significantly correlated with operative time, surgical accuracy, and the learning curve, making it a valid surrogate end point for overall surgical quality. Therefore, a reduction in fluoroscopy frequency with the navigation system, compared with the freehand technique, would support the superiority of the navigation system in terms of surgical efficiency and safety.

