#### Safety Events

The safety end points mainly include the incidence of device-related adverse events, device deficiencies, adverse events, and serious adverse events. These outcomes will be evaluated over the entire follow-up period and are defined as follows:

Device-related adverse event: a problem caused by the test medical deviceDevice deficiency: any issue with the investigational device that could pose an unacceptable risk to patient health or safety during normal use, including deficiencies in labeling, manufacturing, malfunction, or performance failureAdverse event: any negative health change occurring in participants during this study, regardless of whether it is linked to the test deviceSerious adverse event: any adverse event resulting in death, a life-threatening situation, persistent, significant disability or incapacity, requiring hospitalization or extend existing hospitalization, or requiring medical or surgical intervention to prevent permanent damage

All outcomes measures are listed in Table 1.

**Table 1 table1:** Summary of all outcome measures.

Outcome categories and measures			Definition		Assessment time points
Primary outcomes: fluoroscopy frequency			Total number of intraoperative fluoroscopic images acquired during the procedure		Intraoperative period

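### Reduction images count in the primary total although navigation cannot affect them, and nothing keeps the arm from the unblinded surgeon until reduction is finished

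*Protocol article*

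**What the plan says.** **Assignment.** Under Recruitment Strategy and Patient Screening, assignment follows enrolment: "Eligible subjects who meet all criteria will be formally enrolled. They will then be assigned to treatment groups according to the site’s randomization scheme". Under Randomization and Blinding, "Assignment details will be distributed to all participating sites via sequentially numbered, sealed opaque envelopes". The article does not say when an envelope is opened or when the surgeon learns the arm.

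**Blinding.** The same section says that "operating surgeons cannot be blinded because of the distinct intraoperative workflows" of the two techniques.

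**The shared step.** Description of the Novel Device says that "manual reduction will be exclusively used in this study to minimize variability and potential bias". In the control arm, traction reduction under fluoroscopy comes before draping and incision, and ends when the result is judged satisfactory. In the navigated arm the order is the same: "Satisfactory reduction of the fracture fragments is achieved under G-arm fluoroscopic guidance", and only afterwards are the guide pins and reference array placed.

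**The outcome.** Table 1 defines the primary outcome as "Total number of intraoperative fluoroscopic images acquired during the procedure". On where counting starts, the Primary Outcome section says: "This includes each anteroposterior and lateral view obtained, starting from fracture reduction". It also describes the count as not depending on the operator, and plans a separate analysis of each phase (reduction, positioning with the navigation system, placement of implants). Table 2 lists a 3-pin count beside the total.

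**Limitations.** Strengths and Limitations concedes performance bias from unblinded surgeons, but argues that an objective count keeps it small.

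**The concern.** An objective count protects against miscounting. It does not stop the operator from choosing how many views to take. Reduction ends on a judgement, so the number of views before that point is partly discretionary. A surgeon who expects navigation to save images, or who wants it to, could check reduction less often in that arm, or more often in the other, without intending any bias.

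In the phases after reduction the surgeon has to know the arm. During reduction this is not so. The reason given for not blinding surgeons is that the workflows differ, but they are the same until reduction is accepted. An arm difference that arises there is not an effect of navigation, yet it enters the primary comparison in full. Because the assumed effect lies close to the margin, a small difference could decide the trial.

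**Working it through.** **Inputs** (Sample Size section): control 32.2 (SD 5.2), navigated 15.2 (SD 3.7), margin 15.4, one-sided alpha 0.025, power 0.8, 126 evaluable and 150 randomised per group.

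**1. Reproduce the plan.**
- Assumed difference: 32.2 − 15.2 = 17.0. Distance beyond the margin: 17.0 − 15.4 = 1.6 images.
- Sum of variances: 5.2² + 3.7² = 27.04 + 13.69 = 40.73.
- n per group = (1.96 + 0.8416)² × 40.73 / 1.6² = 7.849 × 40.73 / 2.56 = 124.9, so 125 by the normal approximation. The noncentral t gives 126 (power 0.8005).
- Dropout: 126 / 0.85 = 148.2, so 149; the plan uses 150.

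The stated size is reproduced.

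**2. Effect of a pre-navigation shift.** Let b be the mean number of reduction images by which surgeon behaviour alone favours the navigated arm. The documents give no value, so b is assumed. With 126 per group, SE = √(40.73 / 126) = 0.569. If the true difference is exactly 15.4, the probability of claiming superiority is about Φ(b / SE − 1.96). For b = 0.5 this is Φ(0.879 − 1.96) = Φ(−1.08) = 14.0%. The noncentral t gives:

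| Assumed b (images) | 126 per group | 150 per group |
|---|---|---|
| 0 | 2.5% | 2.5% |
| 0.25 | 6.4% | 6.9% |
| 0.5 | 13.9% | 15.8% |
| 1.0 | 41.8% | 48.1% |
| 1.6 | 80.0% | 86.5% |

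The direction is also assumed. A shift against navigation costs power instead: at a true difference of 17.0 with 126 per group, power falls from 80.0% to 48.7% (0.5 image) or 18.2% (1 image).

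**3. Do the planned phase analyses answer this?** The reduction-phase comparison would show an imbalance, but the article does not say what one would mean for the conclusion, and the primary test stays on the total. The other two phases cannot be compared one by one on equal terms. Navigational positioning exists in only one arm, so placement images alone leave out part of what the navigated arm needs to reach the same point. The like-for-like quantity is positioning plus placement in the navigated arm against placement in the freehand arm. The article does not say whether the 3-pin count includes the positioning images.

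**4. Does the margin carry over?** Total difference = reduction-phase difference + post-reduction difference. Absent bias, the first term has expectation zero, because reduction is manual in both arms. The 15.4 margin then applies unchanged to the post-reduction difference. The SD of that count is not given, so its power cannot be stated.

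**The case against.** **Time of disclosure.** A reader might infer that the arm is revealed at enrolment. The documents do not support this. They say that patients are assigned and that assignments travel in sealed envelopes. The screening window in Table 2 includes the day of surgery, so it does not prove advance knowledge either. The opening time may be fixed in the full protocol. If it already comes after reduction, one sentence settles that part. What stands is that this article does not defer disclosure, and that its two reassurances are wrong as worded.

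**Existing safeguards.** Phase counts are planned, and reduction quality and the Garden alignment index are recorded, so early stopping of reduction in one arm might be seen. That is a real partial safeguard. It detects a difference but does not prevent one, and it gives no like-for-like post-reduction comparison.

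**Assumed figures.** The shifts are assumptions, and the error rates are evaluated exactly at the margin. One image is only about 6% of the planned difference (1 / 17.0). The sensitivity comes from the 1.6-image distance, which is a matter of the margin. All of this is fair: the figures show how little shift is needed, not that one will occur.

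**Limited reach.** The participant compensation text carries an exchange rate dated June 15, 2026, and enrolment ends in October 2026. At even accrual (assumed) about 4 of 28 months remain, or 14% of patients. Deferring the envelope therefore helps few of them; the analysis changes reach everyone. Bias in the later phases also remains. Counting every image is defensible when radiation exposure is part of the rationale, so the total can stay primary.

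**Covariate adjustment.** It is tempting to add the reduction count to the primary model for more power. The documents do not support that. They give no share of variance due to reduction, and the count is known to be a pre-allocation measure only where disclosure came after reduction.

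**Conclusion.** The point holds as a design weakness with an inexpensive partial remedy. Assignment precedes surgery, surgeons are unblinded, disclosure is not held back past the shared reduction step, and reduction images enter the primary total. Navigation cannot move those images but the operator can, so the claim of operator independence fails, and objective counting does not answer the concern. With 1.6 images between assumption and margin, an assumed shift of 0.5 or 1 image takes the false-claim rate at the margin from 2.5% to about 14% or 42% (126 per group, the plan's SDs, one-sided 0.025).

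Size and direction of any shift are unknown. The documents do not show that surgeons will behave differently by arm, that the arm is known at enrolment, or that the sample size is wrong.

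**What to change.** 1. **Disclosure.** In Randomization and Blinding, state when the surgeon learns the arm. For patients still to be enrolled, open the sealed envelope only after reduction is accepted and its image count is recorded. Cost: a short amendment, and navigation equipment on standby for every remaining case, including those that turn out to be freehand.
2. **Negative control.** For all patients, prespecify the arm difference in reduction images, with a confidence interval, as a negative control. State how an imbalance limits the conclusion: for example, superiority is not attributed to navigation if the margin is passed only with the reduction-phase difference included.
3. **Sensitivity analysis.** Repeat the primary comparison on all post-reduction images, with positioning and placement added together, against the same margin. Items 2 and 3 use counts already planned and cost only analysis wording.
4. **Text.** Delete the claim of operator independence from Primary Outcome. In Strengths and Limitations, say that objective counting guards against miscounting but not against the operator's choice of how many views to take.

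No extra patients, assessors or procedures are needed.

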**Inclusion criteria**
Aged ≥18 years, regardless of genderDiagnosed with a femoral neck fractureIndicated for and medically fit to undergo internal fixation surgeryProvided written informed consent, either by the patient or their legally authorized representative
**Exclusion criteria**
Prior participation in another clinical trial within the period prior to the primary end point assessmentKnown allergy or hypersensitivity to ≥1 components of the implant materialsDeemed by the investigator to be medically unfit or too frail to tolerate the surgical procedure due to systemic comorbiditiesPresence of active infective foci in the hip or other parts of the body, as determined by the investigatorDiagnosis of metabolic bone disease, radiation-induced bone disease, or similar conditionsSevere hip contracture or significant muscle weakness with long-standing, painless fusion in a functional positionPresence of inflammatory arthritis, such as rheumatoid arthritis, systemic lupus erythematosus–associated arthritis, or ankylosing spondylitisCognitive impairment, inability to comprehend study requirements, or anticipated poor complianceAny other condition that, in the judgment of the investigator, renders the patient unsuitable for study participation

### Trial Intervention Procedures

Eligible participants will be randomized to receive either TCS fixation or NS+TCS fixation.

#### Control Group: TCS Fixation

Following the induction of anesthesia, the patient is placed in a supine position on a traction table. Under fluoroscopic guidance with a G-arm, traction reduction of the FNF is performed until satisfactory reduction is achieved. The surgical site is routinely disinfected and draped in sterile sheets.

A lateral hip approach is made through 3 separate incisions, each approximately 1 cm in length. The skin and subcutaneous tissues are incised sequentially, followed by incision of the tensor fasciae latae and blunt dissection of the muscle. Under fluoroscopic guidance, 3 Kirschner wires are inserted from the lateral aspect of the left thigh, through the FNF site starting above the level of the lesser trochanter, and advanced into the subchondral bone of the femoral head in an inverted triangular configuration. After depth measurement, TCSs are inserted over the guide wires to fix the fracture. Postoperative fluoroscopy is used to confirm satisfactory fracture reduction and alignment, as well as appropriate positioning of the internal fixation screws. The Kirschner wires are then removed. The incision is irrigated thoroughly, and hemostasis is confirmed. After ensuring that the count of surgical instruments and gauze is correct, the incision is closed in layers.

#### Intervention Group: NS+TCS Fixation

Following successful anesthesia, the patient is positioned supine on a traction table. Satisfactory reduction of the fracture fragments is achieved under G-arm fluoroscopic guidance. The operative field is routinely prepared and draped in a sterile fashion.

Two guide pins are inserted, one at the anterior superior iliac spine and another at the lateral femoral condyle, to serve as anchoring points. A navigation reference array is then mounted. The exposed ends of the guide pins are trimmed to an appropriate length to avoid interference with subsequent fluoroscopic imaging. Image registration markers are positioned anteriorly and laterally to the hip joint. Standard anteroposterior and lateral hip radiographs are acquired and uploaded to the navigation system workstation for preoperative trajectory planning for TCS placement. An inverted triangular configuration is selected for dispersed screw placement. After calibration of the navigated drill sleeve, the planned trajectories are used to percutaneously insert 3 guide wires sequentially into the femoral neck and head through small skin incisions. Subsequently, TCS are inserted over the guide wires. Fluoroscopic confirmation is obtained to verify satisfactory screw length and position.

Upon confirmation of adequate fixation, the reference guide pins at the anterior superior iliac spine and lateral femoral condyle are removed. The surgical incisions are irrigated and closed in layers (Figure 3).

**Figure 3 figure3:**
[figure not shown]
Core navigational procedure: (A) placement of the reference array and creation of the surgical incision; (B) planning of screw trajectory, including position, angulation, and orientation; (C) guided K-wire insertion with concurrent depth measurement; and (D) screw implantation.

### Postoperative Management Protocol

Postoperative full weight-bearing may be restricted during the initial 2 weeks for both limbs. Ambulation aids, such as canes or walkers, will be provided according to individual functional needs. Standard deep vein thrombosis prophylaxis will be routinely administered, accompanied by a 3-day perioperative antibiotic regimen to prevent surgical site infection.

### Outcomes and Measures

#### Primary Outcome

The total number of intraoperative fluoroscopic images will be recorded for both groups. This includes each anteroposterior and lateral view obtained, starting from fracture reduction. To minimize observer bias, fluoroscopic counts will be categorized and analyzed separately for fracture reduction, navigational positioning, and implant placement.

Fluoroscopy frequency was selected as the primary outcome for this superiority trial for the following reasons. First, the number of intraoperative fluoroscopic images is an objective, quantifiable, and operator-independent measure that directly reflects the efficiency and precision of guide wire and screw placement. Second, reducing radiation exposure is a major clinical advantage of navigation-assisted surgery, as it lowers occupational radiation risk for surgical staff and potential patient harm. Finally, fluoroscopy frequency is significantly correlated with operative time, surgical accuracy, and the learning curve, making it a valid surrogate end point for overall surgical quality. Therefore, a reduction in fluoroscopy frequency with the navigation system, compared with the freehand technique, would support the superiority of the navigation system in terms of surgical efficiency and safety.

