**(2)**

In these equations, 1–α denotes the significance level, *1–β* represents the statistical power, *Z_1−α_* and *Z_1−β_* are critical values derived from the Z-table, *σ* refers to the SD of the 2 groups, *δ* indicates the mean difference between groups, and *Δ* stands for the superiority margin.

According to published literature, the mean number of intraoperative fluoroscopies in screw fixation for FNFs is approximately 32.2 times [26], while the use of a navigation system is expected to significantly reduce fluoroscopy frequency. On the basis of preliminary pilot data and the experience with navigated procedures at our institution, the mean (SD) number of fluoroscopy images for the control group (nonnavigated) is 32.2 (SD 5.2), and that for the experimental group (navigated) is 15.2 (SD 3.7). The superiority margin was set at 15.4, with a 1-sided significance level of .025 and a statistical power of 0.8.

With a 1:1 allocation ratio between the 2 groups, the sample size calculation was performed using the aforementioned formula and PASS (version 15.0; NCSS LLC) software. Considering patient recruitment feasibility, each group required 126 participants, yielding a total of 252 subjects. After accounting for a 15% dropout rate and distribution across multiple centers, the final sample size was set at 150 (50%) per group, resulting in a total of 300 participants.

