### Statistical Plan

All statistical analyses will be performed using SPSS (version 26.0; IBM Corp), R (version 4.2.0; R Foundation for Statistical Computing), and Origin 2021 (version Origin 2021; OriginLab Corp), with a 2-sided significance level of *P*<.05. For the primary outcome (fluoroscopy frequency), group comparisons will be performed using a 1-sided *t* test or a Mann-Whitney *U* test, supplemented by a linear mixed-effects model with study site as a random effect to account for center-level clustering. Continuous secondary outcomes will be analyzed using similar linear mixed-effects models with baseline covariates, while categorical outcomes will be analyzed using generalized linear mixed-effects models with study site as a random intercept. For outcomes assessed repeatedly at 1, 3, 6, and 12 months, longitudinal mixed-effects models will include fixed effects for treatment group, time, and the group-by-time interaction, along with subject-specific random intercepts and slopes nested within site. Any baseline variable with a standardized difference >0.10 will be adjusted as a covariate. The center-by-treatment interaction will be formally tested; if significant (*P*<.10), exploratory subgroup analyses stratified by site will be conducted. Predefined subgroup analyses include age, gender, Garden classification, and fracture side. Sensitivity analyses will include per-protocol and as-treated analyses.

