### Strengths and Limitations

This trial has several methodological strengths. The multicenter design enhances generalizability across different hospital settings. Prospective randomization with concealed assignment minimizes selection bias. Blinded outcome assessment for patients, radiographic reviewers, and functional assessors reduces detection bias. The sample size calculation was based on published literature [27] and a prespecified superiority margin, ensuring adequate power for the primary outcome.

Several limitations should be acknowledged. First, operating surgeons cannot be blinded because of the distinct intraoperative workflows associated with the navigation system and the freehand technique, which may introduce performance bias. However, the primary outcome is an objective, quantifiable measure that minimizes the impact of this bias. Second, the 12-month follow-up period may be insufficient to detect very late complications, such as osteonecrosis of the femoral head, which can occur beyond 1 year. Finally, all participating centers are in China, and findings may not be directly generalizable to health care systems with different surgical training practices or equipment.

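### The image count is justified as independent of the operator, which the protocol's own text contradicts, and the primary mixed model has no term for the operating surgeon

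*Protocol article*

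**What the plan says.** Under Primary Outcome, the first reason for choosing fluoroscopy frequency is that it is an "objective, quantifiable, and operator-independent measure that directly reflects the efficiency and precision of guide wire and screw placement". The third reason, in the same paragraph, is that "fluoroscopy frequency is significantly correlated with operative time, surgical accuracy, and the learning curve".

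Randomization and Blinding states that operating surgeons cannot be blinded. Strengths and Limitations accepts that this may introduce performance bias, then sets the point aside: "However, the primary outcome is an objective, quantifiable measure that minimizes the impact of this bias".

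Under Statistical Plan, the primary comparison is a one-sided t test or Mann-Whitney U test, "supplemented by a linear mixed-effects model with study site as a random effect to account for center-level clustering". The other models described there have site or subject random effects. None has a surgeon term. The operator appears once, under Allocation: sites with more than half the total sample get subgroup analyses stratified by investigator. That analysis is conditional and is not part of the primary test.

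**The concern.** The rationale contradicts itself. A learning curve belongs to the person operating, so a measure correlated with it is not independent of the operator. The intervention descriptions point the same way: reduction proceeds under fluoroscopy until it is satisfactory, screw position is then confirmed by fluoroscopy, and no number of images is fixed.

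Two separate things follow.

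- **Bias.** Objective counting guards against error by the person who counts. It does not guard against an unblinded surgeon who, knowing the arm, images more or less freely. That would shift the estimated difference.
- **Variance.** Counts from the same surgeon are likely to be alike. The plan recognises clustering but stops at the centre. Depending on how surgeons are spread over the arms, leaving surgeon out costs some precision or, in particular circumstances, understates the standard error.

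Both matter more than usual because the assumed difference lies only 1.6 images beyond the superiority margin.

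**Working it through.** **Inputs from Sample Size.** Control mean 32.2 (SD 5.2); navigated mean 15.2 (SD 3.7); 1:1 allocation. "The superiority margin was set at 15.4, with a 1-sided significance level of .025 and a statistical power of 0.8". The assumed difference is 32.2 − 15.2 = 17.0, which is 17.0 − 15.4 = 1.6 images beyond the margin.

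**Step 1: reproduce the plan's figure.** n per arm = (1.96 + 0.842)² × (5.2² + 3.7²) / 1.6² = 124.9, so 125 by normal approximation. The noncentral t distribution gives 126 (power 0.8005), as stated. 126 / 0.85 = 148.2, so 149, which the plan rounds to 150.

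**Step 2: standard error with surgeon ignored.** Pooled SD = √((5.2² + 3.7²)/2) = 4.513. SE at 126 per arm = 4.513 × √(2/126) = 0.569.

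**Step 3: effect of surgeon clustering.** The number of surgeons, their assignment to arms and the ICC are not given, so the values below are assumptions. True SE = 0.569 × √DE, where DE is the design effect. The actual one-sided error of the unadjusted test is 1 − Φ(1.96 × 0.569 / true SE). The power of a correctly calibrated test is Φ(1.6 / true SE − 1.96). m is the number of cases per surgeon per arm.

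*(a) Surgeons operate equally in both arms, DE = 1 − ICC:*

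| ICC | True SE | Error of unadjusted test | Power, unadjusted | Power, surgeon modelled |
|---|---|---|---|---|
| 0.05 | 0.554 | .022 | 81.0% | 82.3% |
| 0.10 | 0.539 | .019 | 81.6% | 84.3% |
| 0.20 | 0.509 | .014 | 83.0% | 88.2% |

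The unadjusted SE is too large by 3% to 12% (for example 0.569 / 0.509 = 1.12). Against the planned 80%, modelling surgeon gives about 82–88%. Against the unadjusted test under the same conditions, the gain is about 1 to 5 percentage points.

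*(b) Surgeons operate in both arms, patients randomized irrespective of surgeon.* Simulation with 20 surgeons, blocks of 4 and 252 patients gave a one-sided error of .022 to .026 for ICC 0.05 to 0.20. The SE is right on average.

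*(c) Each surgeon operates in one arm only, DE = 1 + (m − 1) × ICC.* With ICC 0.05 and m = 12.6 (ten surgeons per arm), DE = 1.58, SE = 0.715, error .059 and correctly tested power 61%.

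*(d) Surgeons operate in both arms and the treatment effect varies by surgeon, DE = 1 − ICC − s + m × s,* where s is the surgeon-by-treatment share of variance. With ICC 0.05 and m = 12.6, s = 0.02 gives DE 1.182, SE 0.618, error .036 and power 74%; s = 0.05 gives DE 1.53, SE 0.703, error .057 and power 62%.

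**Step 4: how much bias the design can absorb.** A shift of one image per operation is used as an illustration; it is not a figure from the protocol. If the true difference equals the margin and imaging behaviour adds one image in favour of navigation, the one-sided error is 1 − Φ(1.96 − 1/0.569) = 1 − Φ(0.20), about .42. If early navigated cases instead reduce the 17.0 difference by one image, power is Φ(0.6/0.569 − 1.96) = Φ(−0.91), about 18%.

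**The case against.** A reader might infer that, with surgeon omitted, the standard error of the primary comparison is simply wrong. The documents do not support that. Patients are randomized individually, and nothing says that surgeons are tied to an arm. With surgeons in both arms the SE is about right or conservative (cases a and b). The inflated error rates in cases c and d need arm-specific surgeons or a treatment effect that varies by surgeon, and the protocol establishes neither. The site random effect may also absorb part of the between-surgeon variance. This objection stands.

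A reader might also run the two problems together and expect a surgeon term to cure performance bias. It would not: a random intercept deals with variance, while biased imaging moves the estimate. Nor does the text say that the surgeon decides every image; that is an inference from the procedure descriptions.

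It can further be said that lack of blinding and possible performance bias are already disclosed, and that surgeon-level modelling may be left to a full protocol or analysis plan not shown here. The disclosure is real, but its next sentence discounts the problem on a ground that does not hold. The article also does not leave the model open: it names site as the random effect for the primary outcome. So the false rationale remains, and so does the case for improving the stated model.

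**Conclusion.** The point holds as a correction to the rationale and a cheap improvement to the model, not as a demonstrated error in the primary test. The operator-independence claim is contradicted by the same paragraph and by the protocol's statements on blinding and performance bias. The limitation paragraph leans on objectivity that protects the counting, not the decision to image. With a 1.6-image gap and an SE of 0.569, modest performance bias or learning-curve dilution could change the conclusion, but the documents give no basis for estimating either.

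On variance, the direction depends on how surgeons are allocated, which is not stated. The precision gain rests on balanced crossing, an assumed ICC of 0.05 to 0.20 and the plan's SDs as total SDs. Protection of the error rate matters only in cases c and d, and case d needs the surgeon-by-treatment term rather than the intercept alone.

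**What to change.** 1. Under Statistical Plan, add operating surgeon within site as a random intercept in the primary mixed model and in the operative-time and blood-loss models.
2. Prespecify two sensitivity analyses: one with a surgeon-by-treatment random effect, and one with the surgeon's running number of navigated cases as a covariate.
3. State whether the same surgeons operate in both arms.
4. Under Primary Outcome, delete *operator-independent*.
5. Under Strengths and Limitations, replace the reassurance with a statement that objective counting does not remove performance bias, and that the surgeon term does not remove it either.

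Cost: surgeon identity and case order must be recorded for each operation, which operative records should supply, and the model becomes slightly more complex. The abstract reports that no data analysis has been performed, so the change can still be prespecified.
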